## Abstract

**Background:**

Current nutritional management of infants born very preterm results in significant deficiency of the essential fatty acids (FAs) arachidonic acid (ARA) and docosahexaenoic acid (DHA). The impact of this deficit on brain maturation and inflammation mediated neonatal morbidities are unknown. The aim of this study is to determine whether early supply of ARA and DHA improves brain maturation and neonatal outcomes in infants born before 29 weeks of gestation.

**Methods:**

Infants born at Oslo University Hospital are eligible to participate in this double-blind randomized controlled trial. Study participants are randomized to receive an enteral FA supplement of either 0.4 ml/kg MCT-oil™ (medium chain triglycerides) or 0.4 ml/kg Formulaid™ (100 mg/kg of ARA and 50 mg/kg of DHA). The FA supplement is given from the second day of life to 36 weeks’ postmenstrual age (PMA). The primary outcome is brain maturation assessed by Magnetic Resonance Imaging (MRI) at term equivalent age. Secondary outcomes include quality of growth, incidence of neonatal morbidities, cardiovascular health and neuro-development. Target sample size is 120 infants (60 per group), this will provide 80% power to detect a 0.04 difference in mean diffusivity (MD, mm^2^/sec) in major white matter tracts on MRI.

**Discussion:**

Supplementation of ARA and DHA has the potential to improve brain maturation and reduce inflammation related diseases. This study is expected to provide valuable information for future nutritional guidelines for preterm infants.

**Trial registration:**

Clinicaltrials.gov ID: NCT03555019. Registered 4 October 2018- Retrospectively registered.

## Background

Preterm birth is the leading cause of child mortality in high and middle-income countries [1]. Very preterm infants need a combination of enteral and parenteral nutrition to meet their nutritional requirements during hospitalization. Replacing the nutrition provided by the placenta has proven difficult, resulting in postnatal growth restriction [2]. Growth and maturation of organs during the last trimester rely on a steady supply of nutrients. Inadequate supply may lead to neurodevelopmental impairment, chronic lung disease, altered host defense, hypertension, and insulin resistance [3, 4]. The main target for feeding preterm infants is to achieve growth resembling normal fetal growth rates [5] as well as satisfactory functional development [6]. Despite established international recommendation, the nutritional management varies considerably between countries, hospitals, and even within institutions [7, 8]. Training in use of parenteral nutrition (PN) and standardization of nutritional management is important to improve the implementation of nutritional guidelines [8]. Improving the quality and quantity of nutrition provided to extreme premature infants during their critical period of somatic growth and metabolic programming may be pivotal for short-term clinical outcomes as well as long-term neurodevelopmental, cardiovascular and metabolic health. In 2010 a randomized, controlled trial conducted in our institution (the PRENU study) investigated the effect of enhanced nutrient supply, including arachidonic acid (ARA) and docosahexaenoic acid (DHA), in very low birth weight (VLBW) infants compared to standard diet. The intervention group showed significant higher in-hospital growth rates and catch-up growth in head circumference (HC) from birth to 36 weeks PMA [9] as well as improved brain maturation on Magnetic Resonance Imaging (MRI) at term equivalent age (TEA) [10]. Of note, this study was discontinued early due to a high occurrence of a refeeding like syndrome among the intervention infants [11]. The risk of refeeding like syndrome has been confirmed by others [12–15] and the early need for phosphate and potassium supplementation is highlighted in the revised European guidelines on Pediatric Parenteral Nutrition [16, 17]. Moreover, this underlines the importance of conducting well-designed trials on nutritional management in this patient population.

The long chain polyunsaturated fatty acids (LC-PUFAs) linoleic acid and α-linolenic acid are essential fatty acids (FAs) that must be supplied through the diet [18]. They provide energy and are used as precursors of the LC-PUFAs; ARA, DHA and eicosapentaenoic acid (EPA). Particularly ARA and DHA accumulate in the brain during the last trimester and the first postnatal months, i.e. the period of rapid growth and brain development [19]. DHA is one of the main building blocks of the central nervous system including retina and comprises 30–50% of neuronal plasma membranes by weight [20]. Extremely premature infants have low endogenous capacity for conversion of linoleic acid and α-linolenic acid to ARA, DHA and EPA [21]. The lack of adipose stores and limited provision of essential fatty acids through the parenteral solutions increase the risk of depletion. DHA deficiency may lead to reduced visual function and alterations in behavior or cognitive performance [22]. DHA and ARA supplementation in very preterm infants have shown positive effects on growth, visual function and mental development [23].

LC-PUFAs are not only essential cellular building blocks and important sources of energy, but they also act as signal molecules, important in sustaining and resolving inflammation [24]. Studies show that immature infants have elevated levels of inflammatory cytokines during the neonatal period, and that upregulated cytokine expression is associated with the development of bronchopulmonary dysplasia (BPD), patent ductus arteriosus (PDA), retinopathy of prematurity (ROP), necrotizing enterocolitis (NEC), white matter injury (WMI) of the brain and impaired neurodevelopmental outcomes [25–29]. A proposed mechanism behind this up-regulated immune response is sustained activation and impaired resolution of inflammation [27]. There is growing evidence that in addition to structural effects on growth and organ development, supplementation with ARA and DHA, may reduce the incidence or severity of BPD, ROP, NEC and WMI by modulating the immune response [30–32]. Both omega-6 (ARA) and omega-3 LC-PUFAs (DHA, EPA) serve as precursors for the synthesis of bioactive mediators involved in immune modulation. ARA is a precursor of pro-inflammatory mediators (such as leukotrienes of the n-4 series), and of prostaglandins and thromboxanes of the n-2 series, which increase the vascular tone and promote platelet aggregation. However, ARA is also a precursor of lipoxins which are inflammation resolving mediators. Metabolites from DHA and EPA can modulate inflammation by decreasing the production of pro-inflammatory cytokines (TNF-α, IL-1β and IL-6) through the peroxisome proliferator-activated receptor (PPAR) pathways. This in turn inhibits the nuclear transcription factor κB (NF-κB) and increases the production and secretion of anti-inflammatory eicosanoids such as interleukin-10 [32]. Resolvins, protectins, and maresins formed from both DHA and EPA evoke anti-inflammatory and pro-resolving mechanisms, and they enhance microbial clearance [31].

Perinatal infections or inflammation processes play an important role in the pathogenesis of several comorbidities associated with preterm birth, such as BPD, PDA, ROP, NEC and WMI [33]. Very preterm infants are susceptible to septicemia, possibly as a result of attenuated innate immune responses [27]. Interestingly, these infants also show signs of sustained systemic inflammation with elevated pro-inflammatory cytokines [25–27, 34]. Septicemia may be defined as “the host’s deleterious and non-resolving systemic inflammatory response to microbial infection” [35]. The host response is similar to the activation triggered by non-infectious tissue injuries like surgery and ischemic reperfusion events [36]. The alarmin molecule, High Mobility Group Box 1 (HMGB1), is an activator of NF-κB and has been recognized as an important mediator of sepsis [36] and lung injury in preterm infants [37]. HMGB1 is released by necrotic cells, and sustains the inflammatory process after the resolution of the early stage of inflammation [37]. As mentioned, one of the anti-inflammatory potentials of Omega 3-PUFAs is the ability to inhibit the activation of NF-κB [32], and thereby possibly modulate an inappropriate inflammatory response.

The pathogenesis of BPD is multifactorial, but intrauterine and postnatal growth restriction is an independent risk factor [38] disturbing pulmonary alveolar and vessel growth [39]. Along with sufficient early supply of protein and energy to promote growth, omega-3 PUFAs seem to protect against lung injury or reduce BPD severity by a DHA dependent activation of the PPAR pathways [37, 40], thereby accelerating lung maturation, pneumocyte growth and vasoproliferation [40]. Studies show conflicting results. Some studies suggest that low DHA blood levels in premature infants are associated with increased incidence of BPD [41] and that fish oil supplementation may improve lung function [42, 43]. However, one study with enteral supplementation with 60 mg/kg/d of DHA did not result in a lower risk of BPD among preterm infants as compared to standard DHA intake and may have even resulted in a greater risk [44]. A controversy is the importance of balancing the amounts of ARA and DHA, since DHA supplementation alone may suppress ARA concentrations. Fetal plasma levels of ARA are high, with an ARA:DHA ratio around 3:1 at the beginning of the 3rd trimester compared to about 2:1 in term infants. A low ARA:DHA ratio in extreme preterm infants (GA < 28 weeks) has been associated with more severe BPD [45].

ROP is a disorder of vascular development of the retina and the main reason for visual impairment in extreme premature infants. As for the lung, both nutritional and inflammatory factors seem to be important mediators in disease progression. DHA is a major structural lipid in retina and accounts for approximately 50–60% of the total fatty acid content within rod outer segments of photoreceptors [46]. Small RCTs have shown that early lipid supply reduces the incidence of ROP in VLBW infants [47, 48]. Two studies have demonstrated a significantly reduced incidence of ROP with fish-oil containing lipid emulsion as compared to standard soybean oil or a soybean and olive oil emulsion [49, 50]. On the contrary, a trial that compared a multicomponent lipid emulsion (soybean oil, olive oil, fish oil and middle chain triglycerides) with a soybean and olive oil emulsion on the prevalence of ROP in extremely premature infants did not show any differences between the groups [51]. Both decreased levels of DHA and ARA were associated with the development of ROP. A recent RCT showed that enteral supplementation with DHA significantly reduced the incidence of stage 3 ROP in premature infants [52].

WMI of the brain accounts for the predominance of neurological sequelae in surviving premature infants, including cerebral palsy and cognitive deficits [53]. The two main mechanisms presumably responsible for the degeneration of immature oligodendrocytes are hypoxia-ischemia and inflammation [54]. WMI of the premature brain include axonal damage, necrosis and periventricular leukomalacia (PVL) and is commonly categorized in diffuse WMI and focal WMI. MRI defined diffuse WMI is poorly understood histopathological, but is thought to mainly result from damaged oligodendrocytes and less from axonal damage [54]. In both forms of WMI an activation of microglia and astrocytes, as a diffuse inflammatory response is common [55]. Clinically, WMI is associated with hemodynamic instability, poor postnatal growth, and inflammation [34, 54], suggesting that measures to optimize nutrition and reduce inflammation might be beneficial in disease prevention. Other common neurologic comorbidities in the preterm infant includes germinal matrix hemorrhages, intraventricular hemorrhages (IVH) and diffuse atrophy, the cause of which are multifactorial. Interestingly, inflammatory microglial and astrocytic activation following IVH has also been shown to be a determinant of white matter brain damage in preterm infants [56], and early increased cytokine levels in serum is associated with the development of IVH [57]. Hence, we hypothesize that supplying the essential fatty acids ARA and DHA will improve both brain maturation on MRI at TEA as well as overall brain MRI morbidity score ad modum Kidokoro [58].

NEC is a serious disease of the intestines in very preterm infants and may lead to intestinal failure or death. As in the above mentioned comorbidities, the pathogenesis is multifactorial and numerous inflammatory mediators seem to play a prominent role [28, 59]. A few studies show reduced incidence of NEC with enhanced early lipid supply to VLBW infants [47, 48], and a systematic review of omega-3 PUFAs for extremely preterm infants found a trend toward a reduction in the risk of NEC [22].

Increasing evidence indicates that preterm birth and intrauterine growth restriction (IUGR) affects endocrine and metabolic adaptation that program cardiovascular diseases and type 2 diabetes in adult life, the smallest neonates having the highest risk [60, 61]. The embryonic and fetal heart development mainly involves the proliferation of mononucleated cardiomyocytes. The proliferative capacity is lost shortly after birth and the continuing heart growth is due to an increase in cardiomyocyte volume. Thus, by the early neonatal period the human heart contains almost the full complement of cardiomyocytes for the rest of life [62]. Altered myocardial structures have been found in association with intrauterine growth restriction and preterm birth [63]. The limited capacity for cellular regeneration within the postnatal heart after injury may have long-term consequences for heart development [64].

Further studies on the optimal fatty acid composition for nutritional therapy in extremely preterm infants are warranted. Based on this, we designed a double-blind RCT to determine whether early and prolonged supply of ARA and DHA improves brain maturation, quality of growth and clinical outcomes in extreme premature infants as compared to our present nutrient supply.

## Methods/design

### Study design

A single center, parallel group, double-blind randomized controlled trial. The intervention group receives a lipid supplement containing DHA and ARA, and the control group receives standard oral lipid supplement consisting of MCT-oil.

### Study population

Inclusion criteria:
Infants born at Oslo University Hospital with GA < 29 weeksLess than 48 h of age at inclusionSigned informed consent documented according to ICH GCP, and national/local regulations

Exclusion criteria
Major congenital malformationsChromosomal abnormalities and other genetic diseases diagnosed prenatally or detected during the study periodCritical illness with short life expectancy

### Intervention

The nutritional management of the study population is standardized. Initially, the infants receive a combination of PN and human milk, with a gradual increase of nutrients in line with international recommendations (Fig. 1). For this study the nutritional supplements Formulaid™ and MCT-oil™ are defined as investigational nutritional products (INPs). Formulaid™ is an oil-based enteral supplement, derived from fungi and microalgae, containing ARA and DHA in a 2:1 ratio. MCT-oil™ (Nutricia) contains medium chain triglycerides, based on coconut- and palm oil, and is currently the standard lipid supplement in our department to enhance enteral energy supply. The increments of human milk are 12–24 mL/kg/day in both study groups. Full enteral nutrition is defined as 170 mL/kg/day of human milk fortified with PreNAN FM 85® (Nestlé) 3 g/100 mL. The standard intravenous solution used for PN in extremely preterm infants in our department is Numeta G13 E™ (Baxter). Numeta G13E contains a soybean and olive oil emulsion very low in ARA and DHA. To improve the intake of these fatty acids in the intervention group, half-strength enteral supplementation with ARA and DHA is started on the second day of life, and advanced to target, i.e. 0,4 ml/kg (ARA 100 and DHA 50 mg/kg/d), from day 4 and onwards. The infants in the control group receive 0.2 ml/kg of MCT-oil with an increase to 0.4 ml/kg on day 4. It is the responsibility of the physicians of the trial to prescribe the study supplements in the infant’s medication chart. The dose is adjusted weekly against the current weight of the infant; birthweight is used until birthweight is regained. The enteral FA supplementation is administrated in the feeding tube as a daily bolus until 36 weeks PMA. If enteral feeds are stopped by any reason, the FA supplement is also withheld, but administration is recommenced as soon as enteral feeds are reestablished. To ensure compliance, the pharmacist allocated to the trial monitors medication charts and number of doses given.

**Fig. 1 Fig1:**
[figure not shown]
Nutritional protocol

### Randomization

For allocation of the participants to the two treatment groups, a computer-generated list of random numbers is used. The randomization is restricted by blocking and stratification. The block size is determined by the statistician (in the range of 4 to 10) and the information regarding the block size is kept in a separate document unavailable to those who enroll patients or assign treatment. To decrease the risk of unbalanced baseline characteristics, we stratify the randomization by growth status at birth (small for gestational age or not). Within each block, the allocation ratio is 1:1. After informed consent has been obtained, the attending physician or local investigator contacts the pharmacy for allocation consignment. In case of multiple births, the infants are allocated to same treatment by randomizing only the first infant.

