### Sample size

We have used data from the PRENU-cohort for our determination of sample size. The PRENU study showed decreased regional white matter mean diffusivity (MD), suggestive of improved maturation of cerebral connective tracts in the intervention group [15]. The MD in the superior longitudinal fasciculi was 1.18 × 10–3 (6.18 × 10–2) in the intervention group and 1.25 × 10–3 (5.70 × 10–2) in the control group. We consider a 0.04 difference in mean MD as clinically significant. With a power of 80% and a significance level of 5%, 36 infants are required in each group (estimated sample size for two-sample comparison of means). Assuming 40% loss to follow-up (20% mortality/withdrawals/unavailability for scans, 20% non-interpretable images), 120 infants need to be included.

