### Statistical analysis

The primary outcome, TBSS analysis of MD in major white matter tracts at TEA, will be performed by one investigator without knowledge of group affiliation. Other MRI based outcomes will be analysed using voxel-based or “region of interest” (ROI) based analyses and connectivity maturation will be assessed using both global and regional network metrics comparing the two groups [75]. To evaluate the differences between groups on secondary outcomes we will use Student’s t test for continuous variables and a χ2 test or Fisher’s exact test for categorical variables. The Mann-Whitney U test will be used for variables not normally distributed. We will also use multiple linear regression analysis to adjust for important covariates in our analyses and methods for repeated measures will be used as well as parametrical and non-parametrical methods where relevant. Nutrient intake will be compared between the two groups and investigated in relation to clinical outcomes, growth, immune- and metabolic response. A *p*-value of < 0.05 will be considered statistical significant. Multiple hypothesis testing will be performed with p-value correction.

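### Siblings of a multiple birth share one allocation, but the sample size and the tests named for secondary outcomes treat every infant as independent

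*Protocol article*

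**What the plan says.** Three statements in the protocol article bear on this.

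- **Randomization.** "In case of multiple births, the infants are allocated to same treatment by randomizing only the first infant". Twins and triplets therefore always sit in the same arm.
- **Sample size.** The inputs are "With a power of 80% and a significance level of 5"% and a target difference: "We consider a 0.04 difference in mean MD as clinically significant". The result is "36 infants are required in each group (estimated sample size for two-sample comparison of means"), then "Assuming 40% loss to follow-up (20% mortality/withdrawals/unavailability for scans, 20% non-interpretable images), 120 infants need to be included". The section mentions no expected share of multiples, sibling correlation or design effect.
- **Statistical analysis.** "To evaluate the differences between groups on secondary outcomes we will use Student’s t test for continuous variables", with chi-square or Fisher's exact tests for categorical variables and Mann-Whitney for non-normal ones. Multiple linear regression and repeated-measures methods are also mentioned, but neither is linked to siblings. For the primary outcome the section names tract-based spatial statistics (TBSS) of mean diffusivity (MD), without a group-level test.

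The Data analysis section adds that the final analyses will be fixed before unblinding.

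**The concern.** Siblings share a mother, usually a gestational age, and many perinatal exposures, so their outcomes can be expected to correlate positively. When they also share an arm by design, the variance of the difference between arms is larger than it would be for the same number of unrelated infants. A test or sample-size formula built on independent infants misses that extra variance.

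At stake are the validity of the p-values and confidence intervals for the secondary outcomes, and the truth of the 80% power figure. The allocation rule, the sample-size method and the named tests are all stated in this one article, and they do not fit together.

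**Working it through.** **Inputs from the Sample size section**

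- Intervention: "1.18 × 10–3 (6.18 × 10–2) in the intervention group"; control: "1.25 × 10–3 (5.70 × 10–2) in the control group". I read means, SDs and the 0.04 difference on one scale (10⁻³ mm²/s), so the SDs are 0.0618 and 0.0570. On this reading the published sample size reproduces.
- Two-sided 5% level. Sidedness is not stated, but a one-sided test gives 28 per group, which does not match.

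**The plan's own figure**

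- Pooled SD = √[(0.0618² + 0.0570²)/2] = 0.0594.
- Normal approximation: n = 2 × [0.0594 × (1.960 + 0.842)/0.04]² ≈ 34.7, so 35 per group.
- Exact noncentral t: 79.2% power at 35 and 80.4% at 36, so 36 per group.
- 36/(1 − 0.40) = 60 per group, 120 in total.

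The published 36 and 120 are thus reproduced under independence and leave almost no slack. Power drops below 80% once the design effect passes about 1.01.

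**Allowing for siblings**

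Treat all multiples as twins. Let f be the share of evaluable infants whose co-twin is also evaluable, and ICC the within-pregnancy correlation.

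- Design effect: DE = 1 + f × ICC.
- Power if clustering is handled (unweighted means): noncentral t with 36/DE infants per group.
- Type I error if clustering is ignored: 2 × [1 − Φ(1.96/√DE)].

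The article gives neither f nor ICC; every value below is an assumption.

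| f | ICC | DE | Power if handled | Type I error if ignored |
|---|---|---|---|---|
| 0.10 | 0.3 | 1.03 | 79.2% | 5.3% |
| 0.20 | 0.3 | 1.06 | 78.0% | 5.7% |
| 0.30 | 0.5 | 1.15 | 74.5% | 6.8% |
| 0.40 | 0.8 | 1.32 | 68–69% | 8.8% |

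The small spread in the last row depends on whether the degrees of freedom are shrunk by DE or left at 70.

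**Discount for lost scans**

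A pair adds clustering to the MRI outcome only if both scans are usable. If the 40% loss falls independently within pairs, f is multiplied by 0.6:

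- 0.20 becomes 0.12; with ICC 0.3, DE = 1.036, power 79%, naive type I error 5.4%.
- 0.40 becomes 0.24; with ICC 0.8, DE = 1.192, power 73%, naive type I error 7.3%.

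Losses that run together within pairs would shrink this discount.

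**Check by simulation**

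With 36 per arm, f of 0.2–0.4 and ICC of 0.3–0.9, the unadjusted t test rejected a true null in 5.7% to 9.6% of runs, which agrees with the formula.

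**The case against.** **Primary outcome.** A reader might infer that type I error is inflated for the primary outcome too. The article does not support that: it assigns the t, chi-square and Fisher tests to secondary outcomes and names no group-level test behind TBSS. An unnamed test cannot be shown to ignore siblings. This objection stands, and the point is conditional there.

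**Both harms at once.** A reader might also infer that the trial suffers low power and inflated type I error together. They belong to different analyses. At a true difference of 0.04, the naive t test still rejects 79.7%, 78.8% and 77.3% of the time at DE 1.06, 1.15 and 1.32; the larger power loss appears only when clustering is handled. This stands as well.

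**Left to the analysis plan.** The final analyses are to be fixed before unblinding, the article is condensed, and its list of methods is open-ended. An unseen plan may already include a family term. That could settle the choice of tests. It cannot make the 80% power correct, because 36 and 120 were derived in this article under independence. The repeated-measures wording is not tied to siblings and fits the article's serial measurements more naturally.

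**Size.** It rests on two assumed inputs and could be about one point of power. A weighted analysis loses less: about 73–79% over f of 0.2–0.4 and ICC of 0.3–0.9, against 81.5% without clustering, on the normal approximation. Adjusting for shared covariates such as gestational age could absorb some of the correlation. At the difference seen in the earlier cohort, 1.25 − 1.18 = 0.07, power is still about 99% at DE 1.32. All of this limits the size. It does not change the direction, and the plan's chosen difference is 0.04, not 0.07.

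**Conclusion.** The point holds in a bounded form. The design puts siblings in one arm, while the sample size and the named secondary-outcome tests take infants as independent. Used as named, those tests have type I error above 5% whenever multiples are present and sibling outcomes correlate positively. Once siblings are handled, 36 evaluable infants per group do not give 80% power at a difference of 0.04 if the design effect exceeds about 1.01.

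The exact size cannot be set from the article. The undiscounted range (f 0.2–0.4, ICC 0.3–0.8) leans high for the MRI outcome. The scan-loss discount is more realistic there, provided losses are roughly independent within pairs. Secondary outcomes recorded in nearly all infants, such as in-hospital morbidities, would lie closer to the undiscounted figures.

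It would go too far to conclude that the trial is seriously underpowered or that recruitment must be extended. Neither follows without the multiple-birth count and a plausible ICC.

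**What to change.** Before unblinding:

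1. Keep a mother (pregnancy) identifier in the analysis dataset.
2. Analyse infant-level outcomes with pregnancy as the cluster: GEE with a small-sample correction, or a mixed model with a random intercept for mother. Use linear models for continuous outcomes and logistic or Poisson models for binary ones. These replace the unadjusted t, chi-square, Fisher and Mann-Whitney tests for inference.
3. Name the group-level test for the primary TBSS analysis and, if it is a permutation test, permute whole pregnancies rather than single infants.
4. Restate the power of 72 evaluable infants with DE = 1 + (share of evaluable infants with an evaluable co-twin × ICC). Take the share from the blinded multiple-birth count and show a stated range of ICC.

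No extra infants are needed if the lower power is reported openly. Restoring 80% would instead require more: at DE 1.06, for example, 36 × 1.06 = 38.2, so 39 evaluable per group and 2 × 39/0.6 = 130 in total.

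The cost is analysis-plan wording, slightly wider intervals and a somewhat lower stated power. Neither allocation nor data collection changes, provided siblings can be linked.
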